## Abstract

**Background:**

The outcome of non-surgical treatment is generally good, but the treatment course can be long and painful with approximately a quarter of the patients acquiring a nonunion. Both surgical and non-surgical treatment can have disabling consequences such as nerve injury, infection, and nonunion. The purpose of the study is to compare patient-reported outcomes after surgical and non-surgical treatment for humeral shaft fractures.

**Methods:**

A pragmatic randomized controlled trial (RCT) is planned with two study groups (SHAFT-Young and SHAFT-Elderly). A total of 287 eligible acute humeral shaft fractures are scheduled to be recruited and randomly allocated to surgical or non-surgical treatment with the option of early crossover due to delayed union. The surgical method within the allocation is decided by the surgeon. The primary outcome is the Disability of Arm, Shoulder, and Hand (DASH) score at 52 weeks, and is assessor blinded. The secondary outcomes are DASH score, EQ-5D-5L, pain assessed by visual analog score, Constant-Murley score including elbow range of motion, and anchor questions collected at all timepoints throughout the trial. All complications will be reported including; infection, nerve or vascular injury, surgical revisions (implant malpositioning, hardware failure, aseptic loosening, and peri-implant fracture), major adverse cardiovascular events, and mortality.

**Discussion:**

The SHAFT trial is a pragmatic multicenter RCT, that will compare the effectiveness of the main strategies in humeral shaft fracture treatment. This will include a variety of fracture morphologies, while taking the dilemmas within the population into account by splitting the population by age and providing the orthopedic society with an interval for early crossover surgery.

**Trial registration:**

Clinicaltrials.govNCT04574336. Registered on 5 October 2020.

**Supplementary Information:**

The online version contains supplementary material available at 10.1186/s13063-022-06317-6.

## Background and rationale

The incidence of humeral shaft fracture is between 13.5 and 20 per 100.000 annually [1, 2]. It is projected that the incidence of humeral shaft fractures will increase due to changing demographics [1]. The fracture demography follows a typical bimodal pattern with young adults injured in sports, vehicular road-traffic accidents, and other high energy traumas and the elderly injured with simple falls, respectively [2]. Considering this demographic difference, the importance of age in terms of patient expectations, upper limb function, and patient-reported outcome measures (PROM) in humeral shaft fracture treatment is not well understood. The most utilized PROM of humeral shaft fractures across age is the Disability of Arm, Shoulder, and Hand (DASH) [3]. Normative data from the general population shows inferior DASH scores with increasing age and suggests that DASH scores of age groups should not be compared [4, 5].

One of the main challenges with humeral shaft fractures is the choice between surgical and non-surgical treatment. Primary surgical treatment provides consistent high union rates, but patients are exposed to the risk of complications such as infection, iatrogenic radial nerve lesion, and rotator cuff injury as well as shoulder impingement [6, 7]. In contrast, union rates from non-surgical treatment can vary from 75 to 100% [8–12]. If nonunion occurs, it is not uncommon for patients to go through a prolonged treatment course up to 8 months before an additional procedure is offered [12, 13]. Although delayed surgical fixation leads to high union rates [14], the PROMs are inferior compared to primary fixation [13, 15, 16]. These observations may suggest that the prolonged course for patients with union problems is unfavorable. However, the challenge is to identify the patients that will benefit from early fixation. A way of determining early onset of union problems in a young cohort is by gently testing the fracture site at 6 weeks [17] and later for the elderly [18]. In 2020, three systematic reviews with meta-analyses [19–21] were published comparing the surgical and non-surgical treatment of humeral shaft fractures. All studies concluded the need for future prospective randomized controlled trials (RCTs) to complement the current literature in determining the optimal management of these fractures. None of the systematic reviews [19–21] included the RCTs from Finland or Iran [13, 22].

To our knowledge, four RCTs have been completed and all trials compared plate osteosynthesis to non-surgical treatment by DASH score and without distinction of age [13, 22–24]. Four RCT protocols [25–28] are registered in clinicaltrials.gov, WHO and ISRCTN registry. Two RCT protocols are comparing plate osteosynthesis to non-surgical treatment and the last two RCT protocols are comparing plate and nails to non-surgical treatment. Adults of all ages are included, except in one RCT protocol [27] that has an upper age limit at 65 years. Furthermore, in one already finished trial, the trial design had to be adjusted from an RCT to a prospective non-randomized comparative trial due to treatment allocation problems as there was a strong physician preference towards the surgical treatment option [29]. A Cochrane review could not demonstrate any difference in union rate between different surgical procedures (intramedullary nail and plate osteosynthesis) [30].

This emphasizes the need for a pragmatic approach of interventions by including usual care of surgical treatment, considering the influence of age as well as accepting early secondary surgery as a part of treatment to improve disability and function after 12 months.

The SHAFT protocol conforms with the Standard Protocol Items: Recommendations for Interventional Trials (SPIRIT) [31, 32].

## Methods: Participants, interventions, and outcomes

### Objectives

To compare surgical fixation of humeral shaft fracture to non-surgical treatment with early identification and treatment of delayed union by a patient-reported outcome after 52 weeks.

The trial population is divided into two age groups due to the changes in DASH score by age [4]. The definition of delayed union differs in the young and elderly population to consider dissimilarity in bone healing rates:SHAFT-Y for the young with an age cut-off of 18 to 64 years. The early identification and treatment of delayed union is set to 6 to 12 weeksSHAFT-E for the elder with an age cut-off +65 years. The early identification and treatment of delayed union is set to 12 to 26 weeks

### Trial design

A pragmatic multicenter, randomized, controlled, outcome assessor-blinded, clinical superiority trials. The steering committee which consist of trauma- and shoulder-elbow surgeons have assessed the pragmatic design using PRECIS-2 [33] which yielded 37 points out of the possible 45 points (Fig. 1). An explanation for each domain score is provided in Appendix 1. This study furthermore collaborates with the NORCRIN Work Package 13 network.

**Fig. 1 Fig1:**
[figure not shown]
Assessment of the pragmatic design using the PRECIS-2

### Material

Two hundred eighty-seven patients (*n*=163 for SHAFT-Y, *n*=124 for SHAFT-E) with a humeral shaft fracture will be equally randomized to surgical treatment or non-surgical treatment in each group. The overall trial flow and timeline of data collection is outlined in Figs. 2a, b and 3.

**Fig. 2 Fig2:**
[figure not shown]
**a** Trial flow for SHAFT-Y. **b** Trial flow for SHAFT-E

**Fig. 3 Fig3:**
[figure not shown]
Timeline and overview of enrollment, interventions, and assessments for SHAFT

### Inclusion criteria

Fracture types 12A-C (OTA/AO classification)Includes minimal displaced extra-articular fracture extensions to the proximal humerus (less than a 1-cm or 45° angulation) [34]2.Treatment within 14 days from trauma3.Age 18–64 years for SHAFT-Y and ≥65 years for SHAFT-E4.Patients must understand the information given and be able to read and speak Danish, Swedish or Norwegian to complete the study paperwork

All fracture extensions involving the distal humerus and displaced fracture extensions involving the proximal humerus will not be included. Isolated fractures to the proximal or the distal end of the humerus are not eligible for screening. The proximal and distal end segments of the humerus are defined by squares of which the sides are the widest length of the epiphysis/metaphysis in question on the anterior-posterior view [35] (Fig. 4).

**Fig. 4 Fig4:**
[figure not shown]
Illustration of the main fracture zone, the extension zone, and the exclusion zones. All fractures must involve the main fracture zone. Fractures can extend to the proximal extension zone, if minimal displaced within the extension zone. Fractures cannot involve the exclusion zones or be displaced within the extension zone. The proximal square is obtained by measuring the widest part of the segment, then measuring the same length from the apex of the proximal segment through the axis of the proximal humerus, this endpoint separates the proximal humerus from diaphysis. The distal square is obtained by measuring the widest part of the segment, then measuring the same length from the most distal part of the trochlea through the axis of the distal humerus, this endpoint separates the distal humerus from the diaphysis

### Exclusion criteria

Inability to give informed consentUndisplaced shaft fracture (less than a cortex-wide displacement in all radiographic planes)Vascular injury in the ipsilateral armPolytrauma (defined as a trauma with one or more concurrent fractures to the upper extremities or other trauma absolute indications for surgical intervention)Pathological fractureOpen fractureBMI > 40Health conditions preventing either treatment

Primary radial nerve palsy (RNP) is not an exclusion criterion as there have not been shown benefits in recovery time with early exploration [36].

### Recruitment

Patients admitted to the emergency department (ED) in any of the trial sites will be clinically examined and plain radiographs will be obtained to confirm the diagnosis. If the patient fulfills the eligibility criteria, they will be informed of the trial by staff and receive written information with patient participation information and “Researchers rights in a health science research project.” They will be given time to consider and will be scheduled for an appointment with research staff within 10 days. If written consent is obtained at the consultation, randomization will occur immediately after.

Patients will be provided with transport allowance to cover the costs for consultations at 26 weeks and 52 weeks. They further accept telephone calls if they miss follow-up visits to promote participant retention and complete follow-up.

### Interim analyses

We will carry out two interim analyses after trial completion of 25% and 50% of the planned number of included patients, separately for the two age groups. We will use the O’Brien-Fleming rule [37] for determining appropriate significance levels for each analysis, which is determined by time of hypothesis testing (*n*=3) and the overall significance level of *α*=0.05. Under these assumptions, the significance levels are 0.0006 for the first interim analysis, 0.0151 for the second interim analysis, and 0.0471 for the final analysis. Interim analyses will be carried out for both the primary endpoint (DASH) and for serious complications (iatrogenic nerve injury, deep infection, major adverse cardiac events (MACE), other major adverse events, and death) and will be conducted by one-sided tests to determine if the improvement in DASH is significantly above 25 points, respectively if the complication rate is at least 20% higher.

A Data Monitoring Committee (DMC) has been organized to monitor and evaluate the data from the interim analyses. The DMC consists of five independent members including the patient representative (PR), two orthopedic researchers, an orthopedic surgeon, and a nurse.

In the event of one group having zero complications, the significance level cannot be computed by a cChi-square test, and the DMC will have to assess the data due to a statistical variation.

In the event of a patient sustaining several complications, the most severe complication will follow the patient. The complications are ranked in a hierarchy model describing the severity and are ranked from most severe to least severe: death, MACE, deep infection with debridement, other reasons for hospitalization, and iatrogenic nerve injury.

The interim analyses will be conducted by a biostatistician, blinded to the treatment allocation. Data will then be presented to the DMC, in means and proportions and be accompanied with confidence intervals. The DMC will have access to the data unblinded, and if at least one of those two conditions is fulfilled or a statistical variation has occurred at an interim analysis the DMC will be asked to investigate the results in detail and present their recommendation to continue or stop the trial. In the event of disagreement with a split decision (one or more casts a blank vote), the steering committee will be involved in discussing the stopping of the trial.

Furthermore, the steering committee will be monitoring recruitment and drop-out. Any modification in design and recruitment will be registered on ClinicalTrials.gov.

If it is observed that inclusion of patients in the two age groups is too slow, it can be decided to pool the age groups and analyze them as one total group instead. If this decision is made before the first interim analysis, the above significance levels will be used for the total group. If the decision is made between the first and second interim analysis, O’Brien-Fleming significance levels for four analyses will be used, resulting in a significance level of 0.0184 for the second interim analysis and 0.0412 for the final analysis. If the decision is made after the second interim analysis, the O’Brien-Fleming significance level for five analyses will be used, resulting in a significance level of 0.0417 for the final analysis.

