### Primary analysis

Descriptive statistics will be used to report demographic data. Demographic data and outcome measures will be tested visually and statistically (i.e., Shapiro Wilks test). Numeric variables will be summarized by means, standard deviations, and 95% confidence intervals (95% CI). Median and interquartile ranges will be used when normal distribution is not met. Categorical variables will be summarized by frequency and proportion. For group comparison with numerical data, a student’s t-test will be used if data is normally distributed, otherwise, a non-parametric test will be used. For categorical data, a chi-square test will be used for group comparison. An intention-to-treat (ITT) analysis of the primary outcome will be conducted by univariable linear regression, including all patients that do not meet the withdrawal criteria, and will be conducted to minimize bias within results. A sensitivity analysis will test the effects of non-adherence to protocol by conducting a per-protocol analysis and includes only patients who comply with the protocol. For missing data points in an outcome measure, a multiple imputation analysis using predictive covariates (age, sex, smoking, alcohol, UCLA activity, ASA grade) [50–52] will be conducted to deal with nonresponse bias. For comparison, we will carry out a sensitivity analysis excluding all the missing values.

Data will be considered statistically significant if *p* values < 0.0471.

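### The interim and final significance levels have the O'Brien-Fleming shape for looks at thirds, but the looks are at 25% and 50%, and the levels do not fit the interim DASH test as written

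*Protocol article*

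**What the plan says.** The Interim analyses section of the protocol article schedules "two interim analyses after trial completion of 25% and 50% of the planned number of included patients", separately for the two age groups. It names the O'Brien-Fleming rule, "which is determined by time of hypothesis testing (*n*=3) and the overall significance level of *α*=0.05", and concludes that "the significance levels are 0.0006 for the first interim analysis, 0.0151 for the second interim analysis, and 0.0471 for the final analysis". The only inputs named are the number of tests and alpha; the timing of the looks is not used.

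The same section says that the interim analyses "will be conducted by one-sided tests to determine if the improvement in DASH is significantly above 25 points", with a parallel criterion for complications. If a criterion is met, "the DMC will be asked to investigate the results in detail and present their recommendation to continue or stop the trial".

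The Primary analysis section carries the last level forward: "Data will be considered statistically significant if *p* values < 0.0471". The Interim analyses section also gives levels for pooling the age groups (0.0184 and 0.0412 for four analyses, 0.0417 for five), again set by the number of analyses.

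**The concern.** An O'Brien-Fleming boundary depends on how much information is available at each look, not only on how many looks there are. Earlier looks need much stricter levels. Levels built for equally spaced looks are therefore too lenient at 25% and 50%, and the set as a whole need not hold the stated overall 0.05. In addition, these levels are meant for repeated tests of one null hypothesis, while the interim DASH test uses a different null (25 points) from the final test (no difference). What is at stake is whether the thresholds that trigger DMC review, and the final criterion in both age groups, have the error-rate meaning that the protocol gives them.

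**Working it through.** **Inputs.** Interim analyses section: looks at 0.25 and 0.50 of planned patients, final at 1; three analyses; overall alpha 0.05; levels 0.0006, 0.0151, 0.0471; interim DASH test one-sided against 25 points. Sample size section: SD 14.91 and N 163 for SHAFT-Y; SD 18.59 and N 124 for SHAFT-E. Assumption: the information fraction equals the fraction of planned patients with the 52-week outcome.

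**Step 1. Where the stated levels come from.** As two-sided p-values they are z = 3.432, 2.430 and 1.985. The classical boundary is z_k = C/√t_k. With C = 1.985 and t = 1/3, 2/3, 1:

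- 1.985 × √3 = 3.44, p = 0.0006
- 1.985 × √1.5 = 2.43, p = 0.0151
- 1.985, p = 0.0471

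So the shape is that of equally spaced looks. The levels are not exact even there: solving for a total of 0.05 at thirds gives C = 2.004 and levels 0.0005, 0.0141, 0.0451.

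**Step 2. Levels for the planned schedule** (two-sided, overall 0.05, by recursive numerical integration):

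| Rule at 25/50/100% | Look 1 | Look 2 | Final |
|---|---|---|---|
| Stated | 0.0006 | 0.0151 | 0.0471 |
| Classical O'Brien-Fleming, C = 1.978 | 0.00008 | 0.0052 | 0.0480 |
| Lan-DeMets O'Brien-Fleming-type spending | 0.000015 | 0.0030 | 0.0490 |

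The classical z-values are 1.978/√0.25 = 3.96, 1.978/√0.5 = 2.80 and 1.978. Against this boundary the stated interim levels are about 8 times (0.0006/0.000076) and 3 times (0.0151/0.0052) too lenient. The stated final level is slightly too strict.

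**Step 3. Overall error if every look tests zero difference two-sided with the stated levels.** Error spent at the three looks at 25/50/100%: 0.0006 + 0.0147 + 0.0398 = 0.0552 (simulation 0.0550 to 0.0552). At exact thirds: 0.0006 + 0.0147 + 0.0370 = 0.0524. Of the 0.52-point excess over 5%, 0.24 points therefore come from the loose constant and 0.28 from the timing. One-sided testing throughout gives 5.40% at 25/50/100%; one-sided interims with a two-sided final give 5.64%. To keep the stated interim levels as two-sided tests of zero difference and hold 5%, the final level would have to be 0.0415.

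**Step 4. Overall error with the interim DASH test as written.** Crossing needs an observed difference of at least 25 + z × SE, where SE = SD × √(2/n per arm) and the one-sided z is 3.239 for 0.0006 and 2.167 for 0.0151:

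- SHAFT-Y, 25%: n = 163 × 0.25/2 = 20.4 per arm, SE 4.67, 25 + 3.239 × 4.67 = 40.1 points
- SHAFT-Y, 50%: n = 40.75, SE 3.30, 25 + 2.167 × 3.30 = 32.2 points
- SHAFT-E, 25%: n = 15.5, SE 6.68, 25 + 3.239 × 6.68 = 46.6 points
- SHAFT-E, 50%: n = 31, SE 4.72, 25 + 2.167 × 4.72 = 35.2 points

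Under no difference the chance of crossing is below 1e-10 at either look. The overall DASH error is then that of the final test alone, about 4.7%.

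**Step 5. Pooling levels.** For pooling between the two looks, the protocol gives 0.0184 at the second interim. That is close to the third of four equally spaced looks (exact 0.0194, at 75% information), although the second look is placed at 50%. The same reasoning from the count alone recurs.

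**The case against.** The strongest reply is that the trial as written is not inflated. The interim DASH tests are one-sided against 25 points and practically cannot be crossed under no difference, so the DASH error is about 4.7%. A reader who sees the mismatch in timing might infer that this protocol runs at 5.5%. The text does not support that: 5.5% holds only if the interims test zero difference two-sided.

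Three further points also stand. Timing is not the whole cause, since the stated levels give 5.24% even at exact thirds. The final 0.0471 is not too lenient in itself; it lies below 0.0480. And a crossing leads to DMC investigation and a recommendation, not to an automatic stop.

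None of this makes the levels correct. The protocol claims the O'Brien-Fleming rule at overall 0.05, and the stated figures are not that rule at the stated times. The reply also exposes a second mismatch: if the 25-point test stays, the final level has been lowered for interim looks that spend almost nothing.

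**Conclusion.** The point holds in a limited form. The stated levels belong approximately to looks at thirds, not to 25% and 50%, and are slightly loose even at thirds. Read as two-sided tests of zero difference, they give about 5.5% overall, an excess of half a percentage point. Read with the interim test as written, the overall DASH error is about 4.7%, and 0.0471 is not derived from any alpha that those interims spend. On neither reading do levels, timing and tested hypothesis fit together. The figures assume information proportional to planned patients with the 52-week outcome, and they leave out the interim complication tests. The practical weight is moderate: the interim levels trigger DMC review, and the confirmatory threshold is slightly conservative for the planned schedule.

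**What to change.** Amend the Interim analyses and Primary analysis sections together.

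1. Recompute the levels for the actual information fractions: classical 0.00008, 0.0052 and 0.0480, or Lan-DeMets O'Brien-Fleming-type spending, which gives 0.000015, 0.0030 and 0.0490 at exactly 25/50/100% and adapts if the looks shift. These are two-sided p-values; halve them for one-sided tests.
2. State that the levels apply to the zero-difference null, and reconcile this with the one-sided 25-point interim criterion. Replacing the numbers alone would leave levels without error-rate meaning for the test they are attached to.
3. Carry the result through to the 0.0471 in the Primary analysis section, and re-derive the pooling levels from the information at each look.

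The cost is a wording amendment and stricter interim triggers for DMC review. The final test becomes slightly easier to pass (0.0480 or 0.0490 instead of 0.0471).

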### Sample size

The two groups (SHAFT-Y and SHAFT-E) require individual sample size calculations. Two standard deviations (SDs) were obtained from the data of the FISH trial [13] and were separated in age groups of 18–64 years and 65 years and above. By the distribution-based approach, one half a SD corresponds to the minimal important change (MIC) [49]. The calculations are powered to detect a MIC of 7 points in the young and 10 points in the elderly group in DASH, respectively. Two independent means sample size calculations were performed. For SHAFT-Y the following data were included: mean difference = 7.0, SD= 14.91, *α*= 0.05, and power= 0.8. For SHAFT-E the following data were included: mean difference= 10.0, SD= 18.59, α= 0.05 and power= 0.8. Based on the preceding assumptions and including an attrition of 15%, the total sample size is estimated to 163 patients for SHAFT-Y and 124 patients for SHAFT-E.

The FISH trial [13] experienced 5% attrition, since more sites are involved in SHAFT the attrition is set to 15%.

The steering committee can decide to pool data from both RCTs (SHAFT-Y, SHAFT-E) if recruitment is prolonged.

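### The interim DASH tests use a 25-point null but carry O'Brien-Fleming levels for a zero-difference null, so the final level of 0.0471 pays for efficacy looks that spend almost no alpha

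*Protocol article*

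**What the plan says.** The Interim analyses section schedules the looks, separately for each age group: "We will carry out two interim analyses after trial completion of 25% and 50% of the planned number of included patients". For the levels it states "We will use the O’Brien-Fleming rule", with three analyses and an overall alpha of 0.05, giving "0.0006 for the first interim analysis, 0.0151 for the second interim analysis, and 0.0471 for the final analysis".

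The same section says that the interim analyses of DASH and of serious complications "will be conducted by one-sided tests to determine if the improvement in DASH is significantly above 25 points" or, for complications, if the rate is at least 20% higher. Meeting either condition, or having an arm with no complications, leads the Data Monitoring Committee (DMC) to examine the data and recommend continuing or stopping.

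The Hypothesis section gives the null as no superiority of surgery on DASH at 52 weeks. The Primary analysis section carries the adjusted level forward: "Data will be considered statistically significant if *p* values < 0.0471". The Sample size section states "The calculations are powered to detect a MIC of 7 points in the young and 10 points in the elderly group", with alpha 0.05 and power 0.8. The closing paragraph of Interim analyses extends the same scheme to pooling the age groups, with levels 0.0184 and 0.0412, or 0.0417, depending on when pooling is decided.

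**The concern.** O'Brien-Fleming levels come from the joint distribution of one test statistic computed repeatedly against one null. In this plan the two interim DASH tests have a null of 25 points and the final test has a null of zero. The three tests are not the sequence for which the levels were derived.

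The distance between the nulls is large. 25 points is 25/7 = 3.6 times the SHAFT-Y target and 25/10 = 2.5 times the SHAFT-E target, or 25/14.91 = 1.68 and 25/18.59 = 1.34 planning SDs. No reason is given for the figure. Because 25 is the null value, the observed difference must exceed it by a further margin.

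The word improvement is also not tied to a between-arm contrast or a reference time. Read as change within patients, the test would not compare the treatments.

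At stake are the significance level of the primary comparison and whether the trial has the early efficacy rule that it describes.

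**Working it through.** **Inputs.** SDs 14.91 and 18.59, targets 7 and 10, alpha 0.05, power 0.8, 15% attrition, totals 163 and 124 (Sample size); 1:1 allocation (Randomization); looks at 25% and 50%, levels 0.0006, 0.0151 and 0.0471, one-sided interim tests (Interim analyses).

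**Reproducing the sample size.** n per arm = 2[SD(1.960 + 0.842)/difference]² gives 71.2 (SHAFT-Y) and 54.2 (SHAFT-E). Taking 71 and 54 per arm and multiplying by 1.15, 142 × 1.15 = 163.3 and 108 × 1.15 = 124.2, which match the stated totals. A one-sided calculation gives 132 and 99 and does not match. The final test was therefore planned as two-sided at 0.05.

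**Reproducing the levels.** The O'Brien-Fleming shape for three equally spaced looks is z_k = C√(3/k). With C² = 3.94 (C = 1.985), the two-sided levels are 0.00059, 0.0151 and 0.0471–0.0472, which are the stated ones to rounding. They are levels for a zero-difference null with equal spacing.

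**Observed difference needed, between-arm reading.** SE = SD√(4/N) with N patients analysed at the look; critical difference = 25 + z × SE, with one-sided z = 3.239 (0.0006) and 2.167 (0.0151). Without attrition:

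| Group, look | N | SE | Critical difference |
|---|---|---|---|
| SHAFT-Y, 25% | 40.75 | 4.67 | 25 + 3.239 × 4.67 = 40.1 |
| SHAFT-Y, 50% | 81.5 | 3.30 | 25 + 2.167 × 3.30 = 32.2 |
| SHAFT-E, 25% | 31 | 6.68 | 25 + 3.239 × 6.68 = 46.6 |
| SHAFT-E, 50% | 62 | 4.72 | 25 + 2.167 × 4.72 = 35.2 |

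With 15% attrition at the looks these become 41.4, 32.8, 48.5 and 36.1.

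**Chance of meeting the DASH condition.** P = 1 − Φ[(critical difference − true difference)/SE]. The largest value over both looks, without and with 15% attrition:

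| True difference | SHAFT-Y | SHAFT-E |
|---|---|---|
| Zero | 4e-18; 2e-16 | 1.4e-12; 1.1e-11 |
| Design effect (7; 10) | 7e-13; 6e-12 | 5e-8; 1.7e-7 |
| Twice the design effect (14; 20) | 1.9e-8; 8e-8 | 0.0006; 0.0008 |

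For an 80% chance of meeting the condition at a look, the true difference would have to be about 35 to 46 points (SHAFT-Y) or 39 to 55 points (SHAFT-E), depending on look and attrition.

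**Cost to the final test.** The formal DASH rule spends at most about 1e-11, so the overall level is about 0.0471, and 0.05 − 0.0471 = 0.0029 is given up. Power from the noncentral t distribution at the design effects:

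- SHAFT-Y, 71 per arm: 79.3% at 0.05, 78.6% at 0.0471.
- SHAFT-E, 54 per arm: 79.1% at 0.05, 78.3% at 0.0471.

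**Would replacing 25 by zero be enough?** No. Read as two-sided levels against zero at 25%, 50% and 100%, the stated levels give an overall alpha of about 0.055 (0.0552), and 0.0524 even with equal spacing. Exact two-sided O'Brien-Fleming levels for the actual timing are about 0.00008, 0.0052 and 0.0480.

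**The case against.** The strongest defence is that a very high bar for early efficacy is a legitimate choice. The rule only prompts DMC review, the error is conservative, and the cost is under one percentage point of power. All of this stands. It limits the severity, but it does not justify the final level: a rule that serves only as an alert and spends no alpha gives no reason to reduce 0.05 to 0.0471.

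A reader might infer three stronger things that the document does not support.

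- **That the interim looks do nothing.** The same looks test serious complications, and that condition or a complication-free arm can still bring in the DMC. Only the DASH condition is idle.
- **That the DASH condition can never be met.** The figures hold for the between-arm reading, which is the natural one for a stopping test but is not fixed by the wording. On a within-patient reading the condition could be met. Even between arms it could be met if the true difference were about 35 points or more.
- **That type I error is inflated.** As written, the overall level stays below 0.05.

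The statement that no alpha is spent describes the formal DASH rule only. The DMC sees unblinded means and confidence intervals, and could recommend stopping after a complication trigger.

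**Conclusion.** Wrong as written, and should be fixed; it does not threaten the trial's validity. The stated levels belong to repeated tests of zero difference, and the interim DASH tests have a different null. On the between-arm reading, the DASH condition will practically never be met at effects near those the trial is designed for. The final test runs at about 0.0471 when 0.05 was available, at a cost of about 0.75 percentage points of power.

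This rests on the planning SDs, 1:1 allocation, normal approximations at the looks, 0 to 15% attrition and a two-sided final test. The conclusion does not change within the attrition range.

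**What to change.** In Interim analyses, define the interim DASH contrast as the between-arm difference in DASH at 52 weeks. Then choose one of two routes, before any interim look so that the change cannot appear data-driven.

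- **(a) Alert only.** State that the 25-point rule is a DMC alert outside the group-sequential scheme. Set the final level to 0.05 in Interim analyses and Primary analysis. Revise the pooling levels (0.0184, 0.0412, 0.0417) to match. If a reduced level is still wanted for pooling decided after a look, give it its own justification. Cost: there is no formal early stop for efficacy.
- **(b) Working efficacy look.** Test zero difference at every look, with one sidedness throughout and levels derived for 25%, 50% and 100% (two-sided, about 0.00008, 0.0052 and 0.0480). Revise the pooling levels accordingly. With 72 and 55 completers per arm, power is 80.1% (SHAFT-Y) and 80.2% (SHAFT-E), and the chance of crossing by the second look at the design effect is about 21%. Cost: early stopping becomes possible, with the usual overestimate of effect when it happens.

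Both routes change wording and levels only; neither needs new data collection.
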